### Two-arm design: BI versus usual care

A two-arm design was adopted in order to assess the effects of the BI over and above usual care. However, the clinic sites where recruitment takes place for this study offer patients more options than may be available in other safety net medical settings across the country. This fact coupled with the ethical need to provide referral following screening of dependent patients led to defining the control condition as ECAU. This condition provides a test of whether BI is better than a less expensive but relatively high quality usual-care option, as opposed to being better than no intervention at all (neither systematic screening nor follow-up of screen-positive patients) and, as such, represents a rigorous comparison.

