#### Power analysis

Power analyses were conducted with PASS software version 08.0.5 [61]. For the primary outcome of drug use reduction, we computed power for the last point in time when data are collected from participants. We expect to enroll 1,000 study participants, 500 each per BI and ECAU group. Assuming an overall response rate of 75%, we would have data from 375 individuals per group at 12 months. According to results from the WASBIRT study, the frequency distribution of number of days drugs were used in the past 30 days follows a Poisson distribution. For individuals who received a BI in WASBIRT, at baseline, average days of drug use in the past 30 days were 3.8 for moderate risk users, 7.0 for high risk users who received only a BI, and 8.7 for high risk users who received a BI and brief therapy and/or chemical dependency treatment. Based on these averages, the study would have 89% power to detect as low as a 2.5% reduction in average drug use days for moderate risk users, at a two-sided alpha level of .05, and an R^2^ between BI indicator variable and other covariates of .25. If the R^2^ between the BI indicator variable and other covariates were 0.5 (a conservative assumption), the power to detect as low as a 2.5% reduction in average drug use days for moderate risk users is 74%; the power to detect a 5% reduction in average drug use days is 99%. For high risk users, the power to detect a reduction in drug use of at least 2.5% is higher. The end-status analysis assumed for these power calculations is considerably conservative, as data from earlier points in time are not used. Thus, the proposed study has sufficient power to address the first two specific aims.

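### Power is stated for 12 months but rests on baseline means, an unstated assumption of no fall under ECAU; the printed figures also need an unexplained 30-fold factor

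*Protocol article*

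**What the plan says.** The Power analysis section of the protocol article says that, for drug use reduction, "we computed power for the last point in time when data are collected from participants". The sample is given as "We expect to enroll 1,000 study participants, 500 each per BI and ECAU group", and then "Assuming an overall response rate of 75%, we would have data from 375 individuals per group at 12 months". The outcome model is that "the frequency distribution of number of days drugs were used in the past 30 days follows a Poisson distribution".

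The only means supplied are those of people who received a BI in the earlier state programme: "at baseline, average days of drug use in the past 30 days were 3.8 for moderate risk users". Two larger means are listed for the high risk group: 7.0 days where the BI was the only treatment, and 8.7 days where further treatment was added. From these averages, "at a two-sided alpha level of .05", the section derives three figures for moderate risk users:

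- 89% power for a 2.5% reduction when R² between the BI indicator and the covariates is .25;
- 74% for the same reduction when R² is .5;
- 99% for a 5% reduction when R² is .5.

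No 12-month mean is given, and nothing is said about change over time under ECAU. The section describes its approach as conservative because earlier assessments are left out, and concludes that power is adequate for the first two aims.

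**The concern.** The time point and the input do not match. Power for a 12-month comparison depends on the control mean at 12 months, and the calculation uses a mean measured before any intervention. Some fall under ECAU is plausible on the article's own account. ECAU patients receive their screening result, risk information and a referral list (Study design). The comparator is described as "a less expensive but relatively high quality usual-care option". Entry requires recent drug use (Defining the population). The section on the assessment battery allows that in-person assessments might favour the comparison group.

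If the mean falls, the same percentage reduction corresponds to fewer counts and less information. The printed powers would then not apply to the time point for which they are stated. The reason given for calling the calculation conservative does not touch this assumption, which works in the opposite direction.

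**Working it through.** **Inputs, all from Power analysis:** 375 per arm (N = 750), two-sided alpha .05 (z = 1.960), Poisson count, mean μ = 3.8 days per 30 days, reduction r = 2.5% or 5%, R² = .25 or .5. **Assumed, not in the documents:** a fall in the ECAU mean of 10%, 25% or 50%, giving μ = 3.42, 2.85 or 1.90.

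**Formulas.** T is an exposure multiplier; T = 1 means that μ is used as the 30-day mean.

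- Form A, Wald test in Poisson regression with a binary covariate (Signorini): b = ln(1 − r), V0 = 4, V1 = 2 + 2/(1 − r), power = Φ[(√(N·T·μ·b²·(1 − R²)) − 1.960·√V0)/√V1].
- Form B, log rate ratio: SE² = [1/(375·μ·T) + 1/(375·μ·(1 − r)·T)]/(1 − R²), power = Φ(|b|/SE − 1.960).

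**Step 1: the printed figure from the inputs as written (T = 1).** For r = 2.5%, b = −0.02532 and b² = 0.000641. With R² = .25: 750 × 3.8 × 0.000641 × 0.75 = 1.370, square root 1.171. Then (1.171 − 3.920)/2.013 = −1.366, which gives power of 8.6%. The other two cases give 7.0% and 16.4%. The printed 89%, 74% and 99% are not reproduced. With T = 1, neither one-sided testing nor N = 1,000 helps; both together reach at most about 17%, 14% and 30%.

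**Step 2: what does reproduce it.** With T = 30, the same line becomes √41.10 = 6.411, then (6.411 − 3.920)/2.013 = 1.238, which gives 89.2%. The other two cases give 74.3% and 99.95%. Form B gives 89.0%, 73.9% and 99.95%. All three printed figures therefore match once the information is multiplied by a further 30.

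**Step 3: effect of a lower 12-month ECAU mean** (Form A / Form B, %).

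| Scale | ECAU mean | 2.5%, R² .25 | 2.5%, R² .5 | 5%, R² .5 |
|---|---|---|---|---|
| T = 30 | 3.80 | 89.2 / 89.0 | 74.3 / 73.9 | 99.95 / 99.95 |
| T = 30 | 3.42 | 85.9 / 85.6 | 69.8 / 69.4 | 99.9 / 99.9 |
| T = 30 | 2.85 | 79.1 / 78.8 | 62.0 / 61.5 | 99.5 / 99.5 |
| T = 30 | 1.90 | 62.0 / 61.5 | 45.7 / 45.2 | 96.1 / 95.9 |
| T = 1 | 3.80 | 8.6 / 8.4 | 7.0 / 6.9 | 16.4 / 15.8 |
| T = 1 | 1.90 | 6.2 / 6.1 | 5.4 / 5.2 | 10.4 / 10.0 |

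On the T = 30 scale, the first figure drops below 80% at a fall of about 23%.

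**Step 4: what 375 per arm can detect (T = 1, Form A, 80% power).** At a mean of 3.8, the reduction needed is about 11.5% (R² .25) or 14% (R² .5). At a mean of 1.9, it is about 16% or 19%.

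**The case against.** Five points can be made for the plan.

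- **The fall is not documented.** No 12-month ECAU mean is given. The description of ECAU as a good comparator says nothing about its effect on use, and the section on keeping assessment brief says that 30 minutes of assessment has been shown to have no intervention effect. This stands: a fall is plausible, but its size is unknown, and the 10% to 50% range is illustrative.
- **3.8 is the lowest of three means.** The trial enrols the full severity range, and means of 7.0 and 8.7 stay above 3.8 after falls of up to 46% (1 − 3.8/7.0) and 56% (1 − 3.8/8.7). This stands for high risk users. The 89% and 74%, however, are stated for moderate risk users. With T = 1, even 7.0 and 8.7 days give only about 12% and 14% for a 2.5% reduction at R² .25.
- **Direction depends on scale.** If the target were a fixed 0.095 days (2.5% of 3.8), a lower mean would raise power: on the T = 30 scale, 89% becomes about 92% after a 10% fall and 99.5% after a 50% fall. The section states its effect as a percentage, so the fixed-difference reading is the less natural one.
- **Earlier assessments are unused.** This is true and may add some power, but it does not make a baseline mean a 12-month mean.
- **It is a planning assumption, not a slip of arithmetic.** That is fair for the choice of mean. The arithmetic problem is the factor of 30.

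A reader might infer from the T = 30 rows that the trial really has 62% to 86% power for a 2.5% reduction and that only a slight downward adjustment is due. The stated inputs do not support this, because those values carry the unexplained multiplier. Nor do the documents show that ECAU use will fall by any given amount.

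**Conclusion.** The point holds, as the secondary of two problems in one calculation. Power is claimed for 12 months on baseline means, so an unchanged ECAU mean is assumed without being stated. For the percentage reduction that the plan uses, any fall lowers power. On the printed scale the cost is about 3 to 27 points (R² .25) or 4 to 29 points (R² .5) for assumed falls of 10% to 50%, and the 5% claim barely moves.

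The larger gap is between the printed figures and the stated inputs: about 80 points (89% against 8.6%) and 67 points (74% against 7.0%). That the 30-day window was counted twice is inferred from the match of all three figures; the article does not state the exposure setting. The results rest on the Poisson model, 375 per arm and the R² values as given. They show that the power claims for 2.5% and 5% reductions are unsupported, not that the trial cannot detect larger reductions.

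**What to change.** Redo the calculation once, with both corrections together, since either alone leaves the other in place:

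1. Use 3.8 as the mean count per 30 days, so that the window enters once, and state the exposure setting.
2. Replace the baseline mean with an expected 12-month ECAU mean, taken from the earlier programme's follow-up data if available. Otherwise show a stated range, such as 1.9 to 3.8 days, and report the lowest resulting power.
3. Restate either the power or the percentage reduction detectable with 375 per arm. Remove the 89%, 74% and 99% figures, and the conclusion that power is adequate, if the new results do not support them.

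The work is one recalculation and a short rewrite of the paragraph. The cost is that the stated power becomes much less favourable. The correction itself requires no change to enrolment.

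### The printed power of 89%, 74% and 99% does not follow from the stated inputs; under them, power for a 2.5% reduction is about 7–9%

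*Protocol article*

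**What the plan says.** Everything needed for the check is in the Power analysis section of the protocol article (under Data analysis).

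- Sample: "We expect to enroll 1,000 study participants, 500 each per BI and ECAU group".
- Analysed at the final visit, after allowing for loss to follow-up: "Assuming an overall response rate of 75%, we would have data from 375 individuals per group at 12 months".
- Distribution: "the frequency distribution of number of days drugs were used in the past 30 days follows a Poisson distribution", on the basis of an earlier state programme.
- Baseline level: "average days of drug use in the past 30 days were 3.8 for moderate risk users". For two groups of high-risk users the means are 7.0 and 8.7.
- Test: "at a two-sided alpha level of .05".
- Results: "the study would have 89% power to detect as low as a 2.5% reduction in average drug use days for moderate risk users" when the R² between the treatment indicator and the covariates is 0.25. When that R² is 0.5, "the power to detect as low as a 2.5% reduction in average drug use days for moderate risk users is 74" percent, and 99% for a 5% reduction.
- Comment: "The end-status analysis assumed for these power calculations is considerably conservative", the reason given being that earlier assessments are left out. The section then concludes that power is enough for Aims 1 and 2.

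**The concern.** The claimed effect is very small for the sample. A 2.5% cut from 3.8 days is 0.025 × 3.8 = 0.095 day in a month. A Poisson count with mean 3.8 has a standard deviation of √3.8 ≈ 1.95 days, about 20 times that difference. With 375 patients per arm, 89% power for such a difference is implausible on its face.

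This is the only power statement the article gives for its primary outcome, drug use. The Background and the section on public-health benefits argue that small effects spread over many patients are worth having. If the power paragraph stands, a null result can be taken as evidence against even a 2.5% reduction, when the trial would miss such an effect more than nine times in ten.

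**Working it through.** **Inputs (all from the Power analysis section).** N = 750 analysed (375 per arm, 1:1); mean μ = 3.8 days per 30-day window; two-sided alpha 0.05, so z = 1.96; reductions of 2.5% and 5%; R² = 0.25 and 0.5.

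**Formula.** Signorini's power for Poisson regression with a binary covariate:

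power = Φ( [√(N·T·μ·b²·(1 − R²)) − 1.96·√V0] / √V1 )

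Here b = ln(1 − reduction). With equal allocation, V0 = 4 and V1 = 2 + 2/exp(b). T is the exposure by which μ is multiplied. For a 2.5% reduction, b = ln 0.975 = −0.02532 and V1 = 4.051. For 5%, b = ln 0.95 = −0.05129 and V1 = 4.105.

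**Step 1: reproduce the printed figures.** They appear with T = 30:

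| Reduction, R² | First term | Argument of Φ | Power | Printed |
|---|---|---|---|---|
| 2.5%, 0.25 | 6.411 | (6.411 − 3.920)/2.013 = 1.238 | 89.2% | 89% |
| 2.5%, 0.5 | 5.235 | (5.235 − 3.920)/2.013 = 0.653 | 74.3% | 74% |
| 5%, 0.5 | 10.605 | (10.605 − 3.920)/2.026 = 3.300 | 99.95% | 99% |

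Solving for T gives 29.3–30.3 from the 89% figure and 29.4–30.1 from the 74% figure, allowing for rounding. The third figure fits only if 99.95% was truncated, so it does not help to identify T.

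**Step 2: use the inputs as stated.** The mean of 3.8 is already a total over 30 days, and each patient supplies one such count at 12 months, so T = 1. T = 30 would credit each patient with 30 × 3.8 = 114 days of use in a 30-day month.

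| Reduction, R² | First term | Argument of Φ | Power |
|---|---|---|---|
| 2.5%, 0.25 | 1.171 | (1.171 − 3.920)/2.013 = −1.366 | 8.6% |
| 2.5%, 0.5 | 0.956 | (0.956 − 3.920)/2.013 = −1.473 | 7.0% |
| 5%, 0.5 | 1.936 | (1.936 − 3.920)/2.026 = −0.979 | 16.4% |

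**Step 3: cross-checks.**
- By hand, ignoring R²: the standard error of the difference is √(2 × 3.8/375) = 0.142 day, so the effect is 0.095/0.142 = 0.67 standard errors. Power of 89% needs 1.96 + 1.23 = 3.19.
- A Wald test on the log rate ratio gives 9.0%, 7.6% and 15.9% for the three cases.
- Simulation of the 2.5% case with R² = 0 gives 10.3%.

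**Step 4: other readings, for a 2.5% reduction at R² = 0.25 unless noted.**
- R² = 0: 10.1%.
- All 1,000 patients analysed: 10.1%.
- One-sided test: 14.6%.
- Information multiplied by five, as if all five assessments were independent: 25.9%.
- High-risk means of 7.0 and 8.7: 12.3% and 14.3%.

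None comes near 89%.

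**Step 5: what the design can detect.** With T = 1, 80% power is reached at a reduction of 11.5% for R² = 0.25 (0.115 × 3.8 = 0.44 day) and 13.9% for R² = 0.5 (0.139 × 3.8 = 0.53 day). For 89% power at a 2.5% reduction and R² = 0.25, N = (1.96 × 2 + 1.2265 × 2.0128)² / (3.8 × 0.02532² × 0.75) ≈ 22,300 analysed patients, about 30 times the 750 expected.

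**The case against.** The best defence accepts the recalculation and disputes the diagnosis and the remedy.

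- **The cause is inferred.** The article prints no exposure setting. With T = 1, a 13% reduction gives 88.8% and 74.1%, which also round to 89% and 74%, so a misprinted effect size could explain those two figures. The two differ only in R², so matching one nearly guarantees the other. This stands as a caution about the cause. It does not rescue the paragraph: it replaces the stated 2.5% with another number and leaves the 99% for a 5% reduction unexplained, since that case has 16% power.
- **The recalculated power is not that of the planned analysis.** Data analysis specifies linear mixed models over all assessments, and the trial enrols the full range of severity. That is correct. The 7–9% is what the paragraph's own end-status Poisson calculation yields, and it should be described that way.
- **Leaving out earlier assessments is conservative.** As a remark about time points this is fair. It cannot offset a roughly 30-fold overstatement of information. Likewise, power is indeed higher for high-risk users, but only 12–14% at R² = 0.25.
- **2.5% is not named as a target effect, and enrolment does not depend on it.** True. The figure is still printed as something the trial can detect, and the conclusion that power is sufficient rests on it.

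Condensation in a journal article is no answer, because the inputs and the results stand side by side in one paragraph.

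**Conclusion.** The concern holds. With the stated inputs, power is 8.6%, 7.0% and 16.4% where the article prints 89%, 74% and 99%. The printed values need about 30 times the information that 750 single 30-day counts contain. A second multiplication by 30 is the most likely cause, but only the software inputs can confirm it.

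The recalculated figures assume that all 750 analysed patients have the moderate-risk mean of 3.8 and that the variance equals the mean. The second assumption is favourable: if the variance were twice the mean (an assumption, not a figure from the article), power for 2.5% at R² = 0.25 would be about 6%. The R² values work the other way, yet R² = 0 still gives only 10%. The conclusion that power is sufficient is therefore unsupported for reductions of 2.5% or 5%.

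**What to change.** Check the exposure entered in the power software and rerun with one 30-day window per patient. In the Power analysis section:

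1. Replace the three powers with 8.6%, 7.0% and 16.4%, or drop them.
2. State that 375 per arm gives 80% power for a reduction of about 11.5% (R² = 0.25) or 14% (R² = 0.5) from a mean of 3.8, assuming Poisson variance and an end-status analysis.
3. Withdraw the 2.5% claim, and tie the statement that power is sufficient to the restated detectable reduction.
4. Delete the remark that the calculation is conservative, or limit it to the omission of earlier assessments.
5. Correct the high-risk statement to match: 12.3% and 14.3% for a 2.5% reduction at R² = 0.25.

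The cost is one rewritten paragraph. Enrolment, follow-up and analysis are unchanged. The stated detectable reduction becomes about five times larger (11.5/2.5 = 4.6; 14/2.5 = 5.6).

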### Data analysis

Analyses will compare outcomes for the BI and ECAU groups following the intent-to-treat principle. If indicated, these models will take into account baseline differences between the two groups. Time trend models will be used to examine temporal effects, specifying time of assessment as a categorical variable (baseline, 3, 6, 9, and 12 months). Because assessments are nested within patients and patients are nested within clinics and interventionists, analyses will be conducted with linear mixed models. Clinics will be treated as fixed effects, as they were purposively sampled. In contrast, interventionists were assigned to patients based on availability when a BI had to be administered. For interventionists, random effects will therefore be specified and tested.

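### The claim that the end-status power is conservative is unsupported: baseline is coded as a response occasion and adjusted for only conditionally, and neither the treatment contrast nor the within-person correlation is given

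*Protocol article*

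**What the plan says.** The Power analysis section computes power at the last assessment only. The sample is stated as "We expect to enroll 1,000 study participants, 500 each per BI and ECAU group", followed by "Assuming an overall response rate of 75%, we would have data from 375 individuals per group at 12 months". For moderate risk users and a 2.5% reduction in drug-use days, it gives 89% power "at a two-sided alpha level of .05, and an R^2^ between BI indicator variable and other covariates of .25", and 74% when that R-squared is raised to 0.5. It then says "The end-status analysis assumed for these power calculations is considerably conservative, as data from earlier points in time are not used", and from there concludes that power is adequate for the first two aims.

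The Data analysis section plans linear mixed models with assessments nested in patients, "specifying time of assessment as a categorical variable (baseline, 3, 6, 9, and 12 months"). It says that differences between the arms at baseline will be taken into account where this is indicated, without giving the form. It names no group-by-time term and no contrast as the BI effect. Neither section gives a correlation between assessments of the same patient.

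**The concern.** The claim gives a reason: earlier data exist and the power calculation ignores them. Whether ignoring them is conservative depends on how the planned model uses them.

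As written, baseline drug-use days are one of five response occasions. If the BI effect is then taken as the arm difference at 12 months minus the arm difference at baseline, the model estimates a baseline difference that randomisation makes zero in truth, and subtracts it. When the baseline-to-12-month correlation is low, this adds more noise than it removes. If the effect is the plain 12-month difference, the earlier visits help almost only through patients who lack a 12-month value. Either way, the existence of earlier data does not establish a considerable margin.

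At stake is the last step in the argument for adequate power. A reader is told that the true power exceeds the printed figures, and the documents give nothing from which that can be checked.

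**Working it through.** **Inputs from the Power analysis section.** 500 per arm at baseline, 375 per arm at 12 months, two-sided alpha 0.05, printed power 89% (R-squared 0.25) and 74% (R-squared 0.5).

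**Assumptions.** rho, the baseline-to-12-month correlation, is not given and is taken over 0.2 to 0.8. Variances are equal across visits. The 375 have all follow-ups and the other 125 have baseline only. The covariate penalty is the same for every contrast.

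**The plan's own figure.** With 3.8 days as the mean per 30 days and N = 750, the Poisson regression form gives Phi(0.0253 × sqrt(750 × 0.25 × 3.8 × 0.75) − 1.960) = Phi(−1.375), about 9%. The printed 89% returns only if the information is multiplied by a further 30: Phi(3.206 − 1.960), about 89%. Whether the 89% follows from its inputs is a separate question and no part of this point. The printed 89% and 74% serve here only as reference levels. The variance ratios below do not depend on them.

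**Variance ratios.** In the mixed model with separate arm means at each visit, the 12-month mean in an arm is estimated by the completers' 12-month mean plus rho × (baseline mean of all 500 − baseline mean of the 375). Relative to the end-status variance (with 375/500 = 0.75):

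- Difference in change, 12 months against baseline: (1 − rho²) + 0.75(1 − rho)²
- Plain 12-month difference: (1 − rho²) + 0.75 rho² = 1 − 0.25 rho²
- 12-month difference with a common baseline mean, or with baseline as covariate: 1 − rho²

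Example at rho = 0.2 for the change contrast: 0.96 + 0.75 × 0.64 = 1.44.

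**Power.** Phi((1.960 + z)/sqrt(ratio) − 1.960), with z = 1.2265 for 89% and 0.6433 for 74%. Example: 3.1865/1.2 − 1.960 = 0.695, which is 75.7%.

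| rho | Change: ratio | from 89% / 74% | Plain 12-month: ratio | from 89% / 74% | Baseline-adjusted: ratio | from 89% / 74% |
|---|---|---|---|---|---|---|
| 0.2 | 1.44 | 75.7 / 58.3 | 0.99 | 89.3 / 74.4 | 0.96 | 90.2 / 75.7 |
| 0.3 | 1.28 | 80.5 / 63.4 | 0.98 | 89.7 / 75.0 | 0.91 | 91.6 / 77.9 |
| 0.4 | 1.11 | 85.6 / 69.5 | 0.96 | 90.2 / 75.7 | 0.84 | 93.5 / 81.1 |
| 0.5 | 0.94 | 90.8 / 76.7 | 0.94 | 90.8 / 76.7 | 0.75 | 95.7 / 85.2 |
| 0.6 | 0.76 | 95.5 / 84.8 | 0.91 | 91.6 / 77.9 | 0.64 | 97.8 / 90.2 |
| 0.7 | 0.58 | 98.7 / 92.9 | 0.88 | 92.5 / 79.4 | 0.51 | 99.4 / 95.4 |
| 0.8 | 0.39 | 99.9 / 98.6 | 0.84 | 93.5 / 81.1 | 0.36 | over 99.9 / 99.1 |

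**Break-even for the change contrast.** Setting its ratio to 1 gives rho² + 6 rho − 3 = 0, so rho = −3 + sqrt(12) = 0.46. Compound symmetry and first-order autoregression give essentially the same values for these three contrasts.

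**Sensitivity to partial follow-up.** Some patients without a 12-month value will have earlier visits, which helps somewhat. The limit is full recovery of all 500. The plain 12-month ratio then cannot fall below 375/500 = 0.75. The change ratio cannot fall below 0.75 × 2(1 − rho), which is 1.2 at rho = 0.2 (power 82.9% from 89%) and reaches 1 at rho = 1/3.

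**The case against.** The strongest reply is that the article never says that the BI effect is a difference in change. The Data analysis section describes how time is coded and says that the arms will be compared. The exact contrast is normally left to the statistical analysis plan, which is not shown. The same model can yield contrasts that lose nothing: the plain 12-month difference, a baseline-adjusted difference, or the average follow-up change, whose ratio under compound symmetry is (1 + 3 rho)/4 − rho² + 0.75(1 − rho)², or 0.84 at rho 0.2 and 0.24 at rho 0.8. The conditional baseline adjustment also leaves room for the remedy proposed here. All of this stands. It rules out saying that the model makes the effect a change score, but it does not supply the support that the printed claim needs.

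Three stronger readings are tempting and should not be drawn:

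- A reader might infer that the written model has less power than the end-status test. That needs both the change contrast and a low rho, and the documents fix neither.
- A reader might use the factor 2(1 − rho), which gives 1.6 and 71.2% power at rho 0.2. That is a completers-only change score. A mixed model also uses the 125 further baseline values per arm, so the loss is smaller.
- A reader might argue that a single group term over all five occasions must lose power, because averaging in baseline shrinks the effect by about a fifth. Averaging also reduces variance. For completers under compound symmetry the factor is (1 + 4 rho)/5, so power falls only once this exceeds 0.8² = 0.64, that is, above rho = 0.55 (roughly 0.43 if dropouts' baseline values are counted). At low rho this reading gains power.

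**Conclusion.** The point holds in conditional form. The statement that ignoring earlier data makes the printed power considerably conservative does not follow from what the article specifies. Across the readings left open, the 12-month variance relative to end status runs from 1.44 to 0.39 for the change contrast and from 0.99 to 0.84 for the plain difference. So the true position could be a loss of about 13 percentage points from the printed 89% (rho 0.2, change contrast), almost no difference, or a substantial gain. The documents do not show that the claim is false for every contrast. For an averaged follow-up effect, or at high rho, end-status power would indeed be conservative.

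These sizes rest on the assumed rho, equal variances, and the 500/375 retention pattern. They treat the printed power as a reference level without endorsing it. The point concerns only how baseline enters the model and what may then be said about power.

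**What to change.** In the Data analysis section, replace the conditional baseline adjustment with a pre-specified one. Either of two forms will do:

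- Keep baseline as a level of time but constrain its mean to be equal in the two arms.
- Use 3, 6, 9 and 12 months as the responses, with baseline drug-use days as a fixed covariate. The list of time levels then drops baseline.

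In both, state that the BI effect is taken from follow-up visits only, and name the visit or average used. At 12 months the variance factor is about 1 − rho², which is never above the end-status value and, under the assumptions above, is below the change contrast at every rho in the table.

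In the Power analysis section, delete the statement that the end-status calculation is conservative. Alternatively, limit it to the baseline-adjusted model and give the range of rho assumed.

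The cost is wording in the model statement and the power paragraph. No new data are needed, because Table 1 already schedules the ASI-Lite, the source of drug-use days, at baseline and at every follow-up.
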